2.) To examine the role of potential moderators and mediators on intervention effectiveness. Exploratory Aim 2a. To evaluate factors that mediate or moderate effectiveness at 6 and 12 months for all enrolled patients. Potential mediating and moderating variables include patient-level (diabetes distress and self-efficacy and sociodemographics) and facility-level (availability of mental health services) factors. Exploratory Aim 2b. To evaluate factors that mediate or moderate effectiveness at 6 and 12 months for patients in the HOPE arm. Factors include adherence (e.g., session attendance), fidelity (ratings of coach effectiveness), and treatment implementation (e.g., goal-setting quality and self-management behaviors).

3.) Evaluate the potential for embedding HOPE in VA primary care settings, using the RE-AIM framework for evaluating effectiveness of behavioral interventions. Exploratory Aim 3a - Reach. Compare clinical and demographic characteristics of participants with those of all potentially eligible patients. Exploratory Aim 3b - Adoption. Qualitatively elicit PACT clinician and participant perceptions of HOPE to prepare for implementation next steps.

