
their intervention materials in the mail. Participants randomized to HOPE will be instructed to complete the consent for voice recording form and return it in a pre-provided postage paid envelope. Randomization will be blocked and stratified by site to assure balance in the number of patients assigned to HOPE or EUC at each facility. Within each site, we will use random blocks of 4 and 6. The random numbers will be generated in SAS PROC PLAN by [name]. The number of patients randomized at each site will be proportional to the number of patients estimated to be eligible for the study at that facility and adjusted as new CBOCs open and their data becomes available. Should a proportional recruitment prove difficult, we will reconsider this practice to ensure that we meet our sample size goals. Conducting EUC: All enrolled participants will receive the EUC procedures at their clinical site pertaining to diabetes care and depressive symptom management. Once participants are consented and enrolled, study personnel will: 1-Send a standardized letter to study participants notifying them of the study findings related to their diabetes A1C levels and depressive symptoms, and a reminder that their PCPs will be notified as per the informed consent (in Sect S as EUC Cover Letter). Patients will also be provided with basic educ. materials related to diabetes and depression (Sect S); 2-Enter a parallel note in the patient's CPRS record notifying the PCP of these findings, with an add'l signer request (to signify awareness of note); 3-Include recs for MH referral or treatment prompt for depression in the CPRS note; Repeat steps 1-3 after the results of the 6mo and 12mo data collection are available. No specific recs for diabetes care will be provided, no further contact will be made during the acute intervention period for participants in EUC. Conducting HOPE Intervention: Study RAs will contact participants randomized to HOPE to arrange the first behavioral call w/in a 2-3 week window. The coach will initiate calls at the participant's time and day of choosing. If a veteran fails to appear 3x for the phone appt, a letter may be sent by the staff on behalf of the coach. Like EUC, HOPE patients will receive basic educ info on diabetes and depression. A standardized behavioral counseling framework is used by coaches to guide each of the calls, regardless of the specific contents of each session. At the conclusion of each behavioral coaching call, the coach will summarize the progress of the current session and schedule the next call. The coach will then enter a note in the participant's CPRS record with the participant's PCP listed as an additional signer. This note will summarize the specifics of what was discussed during the prior coaching call and provide, in the participant's own language, the agreed upon specific goal and action plan(s). Coaches may also suggest additional f/u or referrals to the PCP, based on the participant's needs and requests, such as a referral to a diabetes educator or nutritionist. Coaches may also ask PCPs to schedule a quicker (urgent care) f/u visit if warranted. The actual request for referrals and all medical f/u appts and medication changes will be left to PCPs' discretion. HOPE Intervention modules: A total of 9 sessions will be conducted during a 6mo period. For the first 3mo, coaching sessions will be 30min, take place bi-weekly, and will include 2 core sessions and 4 elective sessions (where patient chooses topic to cover). In the next 3mo, 3 f/u sessions, each 15min long, will occur once a month. There are a total of 6 modules for the patient to choose from for their elective sessions, and modules may last more than one session. The modules assigned to elective sessions 3-6 are adaptable, and one or more may be presented in any order at the participant's and coach's discretion.

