
psychotherapy during the previous 6 months (yes/no), whether psychotropic medications were started or changed during the past 6 months (yes/no), and whether insulin was added during the past 6 months (yes/no). A1c and Depression Outcomes at 6 months--The patients' A1c levels and PHQ-9 scores at 6 months will be the primary outcomes. We will examine the normality of the distributions of these outcomes and will consider transformations such as the log or the inverse, if necessary. Separate models will be run for HbA1c and for PHQ-9. We will run hierarchical linear model analyses to account for the correlation of patients being seen by the same PCP. Using this nested approach, we will test if there are differences between EUC and the HOPE intervention, using the A1c level and the PHQ-9 score (either untransformed or transformed, if needed) as dependent measures. Although patients are also nested within coach, the coaches are not assigned exclusively to certain PCPs. We will include intervention fidelity scores for each coach as a study variable in our analysis of this aim to account for coaching fidelity effects. Each model will contain a variable indicating the treatment group, indicator variables representing site, whether or not the patient was on exogenous insulin (evidence suggests that insulin use impacts both A1c and depressive symptoms), receiving psychotherapy, taking psychotropic meds, and baseline A1c or PHQ-9 levels as independent variables. A significant value for the treatment group variable in the hierarchical model will indicate that there were statistically significant differences between the intervention and EUC. In addition, we will examine whether the groups differed as to whether or not they had clinically significant changes in A1c and PHQ-9 by dichotomizing the outcomes. A significant decrease for A1c is defined as 0.5 between each time point and from baseline to 12-months. For PHQ-9, this will be a change score of 5 or greater at 6- and 12-months. We will test whether the two groups (clinically significant change vs. no change) differed using a hierarchical logistic-regression model in which the dichotomous outcomes are the dependent variable. The independent variables will be those described above for the hierarchical linear regression. A1c and Depression Outcomes at 12-months-- The patients' A1c levels and PHQ-9 scores at 12-months will be the primary outcomes. Similar to the analyses at 6 months, we will examine the distribution and run hierarchical linear models on the 12 month data. In addition, we will examine all of the time periods in a hierarchical longitudinal analysis, separately for A1c and PHQ-9. This random coefficient model will allow us to fit a line for each participant using his/her available data, including participants with missing values, and will maximize the power to detect differences because patients are not removed from the analysis if any of the time periods is missing. Patients will be nested with their PCP. The model will contain the A1c and PHQ-9 values for each of the time periods (baseline, 6 and 12 months). The independent variables in the model will be time, treatment, the interaction of time and treatment, site, and use of exogenous insulin psychotropic meds, or psychotherapy. The treatment effect will measure differences between the intervention and EUC groups at baseline, and the time effect will measure whether there was an overall change over time in the two clinical outcomes. The time-by-treatment interaction is of most interest in the longitudinal analysis because a significant value will indicate that there was a difference between the intervention and EUC groups over the 12-month time period. Mediators and Moderators: To examine the role of potential moderators and mediators on intervention effectiveness, we will evaluate factors that mediate and moderate outcomes at 6 and 12 months. Moderating variables are those that specify on whom and under which conditions treatments have different effects. The moderating variables for this aim include sociodemographic traits, BMI, medical and psychiatric comorbidity, and social support. Mediator variables identify possible mechanisms through which a treatment achieves its effect. Mediators include the GET-D scores for goals and action plans, diabetes-related distress, self-efficacy, performance of self-care behaviors, and adherence to pharmacological therapy. We will consider the difference between the moderators and mediators in terms of when they occur relative to treatment and whether they are correlated with treatment. Moderators must precede treatment and should not be correlated with treatment. Mediators will occur during treatment and should be correlated with treatment. Thus, we will initially test for the association of the moderating and mediating variables with treatment. Since the treatment is a dichotomous variable, we will use t tests to determine if continuous moderators or mediators are associated with treatment and chi-square tests to determine if ordinal or categorical moderators or mediators are related to treatment. After verifying that a possible moderator is not significantly related to treatment, we will run the model, including a term in the model for the moderator and a term for the interaction of that variable with treatment. A significant value for the interaction term will indicate that the effect of treatment on the individual patients depends on their value of the moderator. For mediators, we will test if the variable has either a main or interactive effect on the outcome. With an emphasis on the effect size of treatments and what influences the effect size for a particular moderator or mediator, we will calculate effect sizes at each of the scheduled time points. In addition, we will form response categories to assess the stability of variables under two approaches to measuring outcomes (one using continuous variables for outcomes and the second using categories for the outcomes). For example, we might define an improvement in A1c as a decrease of 0.5 from baseline or PHQ-9 decrease of 5 from baseline. We would then run the analytic models using the dichotomous variable of whether or not the patients' A1c level improved as the outcome variable. If the two-variable presentations prove to be similar, we will likely use the categorical approach because of greater ease in reporting results to

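### Coach fidelity scores are assigned to the two-arm Aim 1 analysis, although only HOPE patients have a coach; this conflicts with the listed covariates and with Aim 2b

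*Protocol*

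**What the plan says.** All references are to the protocol.

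- **G2, 6-month outcomes.** The hierarchical models are two-arm: "we will test if there are differences between EUC and the HOPE intervention". Shortly afterwards, still on the same models, comes "We will include intervention fidelity scores for each coach as a study variable in our analysis of this aim", with the stated purpose of accounting for coaching fidelity.
- **G2, next sentence.** The model is then listed: "Each model will contain a variable indicating the treatment group, indicator variables representing site", followed by insulin use, psychotherapy, psychotropic medication and the baseline value. Fidelity is not in the list.
- **G2, decision rule.** "A significant value for the treatment group variable in the hierarchical model will indicate that there were statistically significant differences" between the arms.
- **G2, other models.** For the dichotomised outcomes, "The independent variables will be those described above for the hierarchical linear regression". The 12-month linear models are to be run like the 6-month ones. The longitudinal model has its own list, without fidelity.
- **G2, a priori adjustment.** The variables fixed in advance for the primary aim are baseline HbA1c and PHQ-9, exogenous insulin and site. Fidelity is absent here too.
- **F1 and F2.** Only the HOPE arm (146 patients, 60%) receives coaching, and patients are paired with a coach after randomisation. The EUC arm (96 patients, 40%) gets letters, educational materials and a note to the PCP; otherwise "no further contact will be made during the acute intervention period for participants in EUC".
- **Section D, Exploratory Aim 2b.** For patients in the HOPE arm: "Factors include adherence (e.g., session attendance), fidelity (ratings of coach effectiveness" and so on.

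**The concern.** The Aim 1 test should compare the arms as randomised. A coach's fidelity score is not a baseline variable: it describes treatment delivery after randomisation, and it has no meaning for an EUC patient. Adding it beside the treatment indicator is not ordinary covariate adjustment, because the score varies only within HOPE and its level in EUC is a matter of coding. That coding decides what the treatment coefficient means, and the decision rule rests on that coefficient for both HbA1c and PHQ-9. An analyst who follows the fidelity sentence and one who follows the covariate list that comes after it would fit different models. The two could report different primary results.

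**Working it through.** **1. The plan's own figures.** Inputs from G1: HbA1c difference 0.5, SD 1.1, d = 0.45, two-sided 5%, power 80%.

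- A two-sample t test at d = 0.45 needs 78.5, so 79 per group and 158 in total, as stated.
- Clustering: 1 + (4 − 1) × 0.05 = 1.15, and 158 × 1.15 = 181.7, so 182.
- Attrition: 182 × 1.33 = 242.

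Applying the 60/40 split of F1 to 182 gives 109 HOPE and 73 EUC. With the 1.15 design effect and no fidelity term, power for 0.5/1.1 is 79.5%. The planned power is therefore that of a model without fidelity.

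**2. Fidelity missing in EUC.** A complete-case fit drops all EUC patients. The intercept, treatment and fidelity columns (three) then have rank 2, so the treatment effect is not estimable. The rank is also 2 if EUC is coded 0 and all coaches have the same score, because fidelity is then a multiple of the treatment indicator.

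**3. EUC given a constant c.** Take y = a + bT + gF, with F = c for every EUC patient and mean fidelity F̄ in HOPE. The arm means give

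b = (ȳ_HOPE − ȳ_EUC) − g(F̄ − c).

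The slope g comes from HOPE alone, so b is the HOPE–EUC difference extrapolated to HOPE coaches with fidelity c. If c = 0 on the raw scale, that is a coach with zero fidelity. If fidelity is centred on the HOPE mean and EUC is set to 0, then F̄ − c = 0 and b is the plain difference between arms.

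**4. Precision.** With s the outcome SD and SD_F the spread of fidelity across HOPE patients,

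Var(b) = s²[1/n_EUC + 1/n_HOPE + ((F̄ − c)/SD_F)²/n_HOPE].

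The base term is 1/73 + 1/109 = 0.02287. The protocol gives no fidelity scale, mean or SD, so the ratio F̄/SD_F is assumed. For c = 0 and a ratio of 4, the added term is 16/109 = 0.14679, and √[(0.02287 + 0.14679)/0.02287] = 2.72. Other ratios follow in the same way. The last column includes the design effect and supposes that the coefficient stays at 0.5.

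| Assumed mean/SD | SE multiplied by | Power |
|---|---|---|
| no fidelity term | 1 | about 80% |
| 2 | 1.6 | 41% |
| 4 | 2.7 | 18% |
| 8 | 5.2 | 8% |

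**5. Meaning of the coefficient.** A simulation used 2000 runs, 109 versus 73 patients, a true average effect of −0.5, SD 1.1, coach-level scores with an assumed mean/SD of 5, EUC coded 0 and no PCP clustering.

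| Dependence of benefit on fidelity | Mean treatment coefficient | Power |
|---|---|---|
| none | −0.50 | 15% |
| half proportional | −0.24 | 7% |
| fully proportional | −0.03 | 5% |

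Leaving fidelity out, or centring it within HOPE with EUC at 0, gave about −0.50 and 84–86% power in all three cases.

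**The case against.** The best defence is that the protocol never plainly makes fidelity a term in the treatment model. It calls the scores a study variable in the analysis of the aim, and the explicit list that follows leaves them out. So do the a priori list and the longitudinal list, and the decision rule comes directly after a list without fidelity. On that reading the tested coefficient is not conditioned on fidelity at all. Moreover, a HOPE-only coach variable can be carried without harm if it is centred within HOPE, and centring is a detail that an SAP may settle.

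Much of this stands. A reader might infer that the primary test is certainly conditioned on fidelity, or that the only possible outcomes are a non-estimable effect or an effect at zero fidelity. The documents support neither: the lists point the other way, and the centred coding is a third case. What does not go away is the sentence itself. It sits among the two-arm models and names the analysis of this aim, and no separate model is described for it. An SAP could supply a coding, but the protocol's own statements would still disagree about what enters the model.

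A reader might also infer the same fault for GET-D, since "Mediators include the GET-D scores for goals and action plans" and mediators are to be tested against treatment. The available text does not say how GET-D is scored or that EUC patients have no scores, so that inference is not supported.

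**Conclusion.** The concern holds as an inconsistency in the primary analysis with a serious consequence under one of its readings. The fidelity sentence cannot be reconciled with the covariate lists in G2 or with the HOPE-arm placement in Section D. If it is followed literally in the two-arm model, the treatment effect is either not estimable or is the effect at whatever fidelity value EUC is assigned. Only the centred coding returns the randomised average effect, and the protocol does not specify it.

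This conclusion rests on the text and on algebra. The size does not: the 2.7-fold standard error and the power figures require an assumed mean/SD ratio, raw scores, EUC coded 0 and entry of the term into the primary model. A reader might take them as the power this trial would have, but the protocol states none of those conditions. They show the direction and possible scale only. The planned sample size is not called into question.

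**What to change.** Delete the fidelity sentence from the Aim 1 analysis in G2. State that the 6-month and 12-month linear and logistic models test treatment using only the listed covariates. The longitudinal model's list needs no change on this point. State that fidelity is analysed only among HOPE patients under Exploratory Aim 2b, where Section D already puts it.

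The cost is a wording change. No data collection, sample size or planned use of the fidelity ratings under Aim 2b is lost, and power under the plan's assumptions stays at about 80%.

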#### Exclusion Criteria:

We will exclude potential participants only for clinical factors that would render a telephone-based behavioral activation intervention inappropriate. Specific exclusion criteria are: (a) lack of regular access to a telephone; (b) significant cognitive impairment (three or more errors) on an established six-item screening exam; and (c) meeting criteria for bipolar, psychotic, or substance-abuse disorders; (d) presence of hearing impairment; (e) their medical chart recommends not titrating therapy due to prior history of significant hypoglycemic events; or (f) they live within 20 miles of the MEDVAMC. Patients will be secondarily excluded if their HbA1C level falls below 7.5% at baseline assessment, or if they report suicidal ideation on the PHQ-9 at baseline assessment.

Patients receiving mental health services for conditions other than bipolar, psychotic or substance-abuse disorders at the time of study recruitment will not be excluded. All mental health treatments and health service-use characteristics will be included in study analyses as covariates.

Coaches do not have any exclusion criteria. All disciplines in primary care are invited to participate.

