Independent Evaluators (IE) who are blinded to the study procedures and treatment assignments will collect data at 6 and 12 months by phone. They will mail assessment packets to participants and then work with them to complete all self-report items. IEs will arrange a lab visit for a blood draw within 2 weeks before and 2 weeks after the target data-collection time (facilitated by PCPs). If PCPs have already obtained A1c levels in that timeframe, those values will be used. Participants will receive modest compensation after A1c results and self-report assessments are collected. RAs will also perform chart abstraction of clinical baseline, moderating, and exploratory variables. Data Quality Assurance: Using previously developed and standardized procedure manuals, providing rigorous training and fidelity measurement of study coaches and independent evaluators, as well as providing written guides for assessments are ways quality will be assured. Attrition/Retention and Missing Data: We expect rates of missing data for primary outcomes less than 25%, leading to primary outcome data for greater than 75% of participants. To evaluate the potential relationship between loss to f/u and outcome variables, reasons for study discontinuation will be recorded for subsequent analyses, and overall attrition rates will be factored in the analyses of the primary specific aim. We will conduct sensitivity analyses using tests for data missing completely at random and tests for nonrandom missingness. We will also plot the data over time to visually assess changes in outcomes from baseline to 12 mos. and to indicate whether additional terms are needed in the models to account for nonlinearity over time. Data Analysis Plan: Primary Analyses: A1c and Depression Outcomes--We will compare participants in the two study arms on baseline characteristics, including sociodemographic characteristics (age, race/ethnicity, gender, education level, independent living status, VA copay status, employment status) and clinical variables (BMI, Deyo comorbidity score, psychotropic and diabetes medications and treatments, specific psychiatric diagnoses, and number of PCP visits in the previous 12 mos). Based on recommendations of the CONSORT group, we will not provide tests of significance or adjust subsequent analyses for variables found to differ because adjustment may bias the estimated treatment effect. However, the analyses for the primary aim will be adjusted for variables we have decided a priori may be important to control: a) baseline values of HbA1c and PHQ-9, b) whether the patient was on exogenous insulin, and c) the stratification variable, site. In addition, we will compare participants on d) access to psychotherapy and medication, defined as dichotomous variables. At baseline, 6 months, and 12 months, we will construct variables for whether the patient was receiving

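### The Aim 1 models adjust for insulin, psychotherapy and psychotropic use without limiting these terms to baseline, and the protocol's covariate lists conflict; post-randomisation values would stop the treatment coefficient estimating the total effect of HOPE versus EUC

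*Protocol*

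**What the plan says.** Protocol section G2 (Data Analysis) describes the covariates for Aim 1 in several places.

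- **A priori list.** G2 first says that "the analyses for the primary aim will be adjusted for variables we have decided a priori may be important to control". It names baseline HbA1c and PHQ-9, exogenous insulin, and site. Access to psychotherapy and medication follows as something on which participants will be compared.
- **Constructed variables.** "At baseline, 6 months, and 12 months, we will construct variables for whether the patient was receiving" psychotherapy in the preceding 6 months, and also "whether psychotropic medications were started or changed during the past 6 months (yes/no), and whether insulin was added during the past 6 months (yes/no").
- **Model terms.** The 6-month model contains treatment group, site, "whether or not the patient was on exogenous insulin (evidence suggests that insulin use impacts both A1c and depressive symptoms"), and then "receiving psychotherapy, taking psychotropic meds, and baseline A1c or PHQ-9 levels as independent variables". The 12-month models follow the same pattern. The longitudinal model also contains insulin, psychotropics and psychotherapy, again with no time point.

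Outside G2, the Exclusion Criteria end with a broader statement: "All mental health treatments and health service-use characteristics will be included in study analyses as covariates".

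F2 (Procedure) describes a route by which coaching could alter co-treatment. After each call the coach writes a record note that the primary care provider (PCP) must sign, and "Coaches may also suggest additional f/u or referrals to the PCP".

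**The concern.** Aim 1 compares the clinical effectiveness of HOPE with that of EUC. In a randomised comparison that is the total effect, including any benefit that arises because a coached patient is referred, seen sooner or has treatment changed. A covariate measured after randomisation and affected by coaching lies on that path, and holding it fixed removes the part of the effect that runs through it. If unmeasured severity also drives co-treatment, conditioning on it links arm and severity as well, and the coefficient then estimates neither the total nor the direct effect.

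This would touch the primary coefficient for both outcomes at both time points, in a trial powered at about 80%. Apart from bias, the lists in G2 and under Exclusion Criteria allow different primary models, and an analyst could defend any of them from the text.

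**Working it through.** **1. The passages side by side**

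| Place in protocol | Insulin | Psychotherapy and psychotropics | Time point |
|---|---|---|---|
| G2, a priori list | adjust | compare only | stated for HbA1c and PHQ-9 only |
| G2, constructed variables | added | received; started or changed | baseline, 6 and 12 months, each with a 6-month look-back |
| G2, 6-month and 12-month models | adjust (status) | adjust | stated for HbA1c and PHQ-9 only |
| G2, longitudinal model | adjust | adjust | none |
| Exclusion Criteria | not named | adjust, plus service use | none |

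At the 6-month visit the look-back window is the active coaching period; at 12 months it is the maintenance period. G2 itself describes mediators as arising during treatment and being correlated with it. A co-treatment variable taken at 6 months that coaching affects would fit that description.

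**2. The plan's own sample size (G1)**

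A two-sample t test with d = 0.45, two-sided alpha 0.05 and power 80% gives 79 per group, 158 in total. Then 158 × 1.15 = 181.7, i.e. 182, and 182 × 1.33 = 242.06, i.e. 242. The chain reproduces and is not in dispute.

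For power at the planned 60:40 allocation, with 25% attrition and a design effect of 1.15, the effective sizes are 146 × 0.75 / 1.15 = 95.2 and 96 × 0.75 / 1.15 = 62.6. With a difference of 0.50 and SD 1.1, power is 79.3%.

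**3. What adjustment for an affected co-treatment would do**

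In a linear model with no unmeasured common cause of co-treatment and outcome:

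adjusted effect = total effect − (arm difference in uptake) × (effect of co-treatment on HbA1c)

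The total effect of 0.50 and SD of 1.1 come from G1. The uptake differences and co-treatment effects are assumptions, because the protocol gives none. Power keeps the standard error from step 2.

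| HOPE minus EUC uptake | HbA1c reduction from co-treatment | Adjusted effect | Power |
|---|---|---|---|
| 0 points | any | 0.50 | 79.3% |
| +5 points | 0.3 | 0.50 − 0.05 × 0.3 = 0.485 | 76.8% |
| +10 points | 0.5 | 0.50 − 0.10 × 0.5 = 0.45 | 70.5% |
| +20 points | 0.5 | 0.50 − 0.20 × 0.5 = 0.40 | 60.3% |
| +30 points | 0.8 | 0.50 − 0.30 × 0.8 = 0.26 | 30.3% |
| −7.7 points | 0.5 | 0.50 + 0.077 × 0.5 = 0.54 | not computed |

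**4. With unmeasured severity driving uptake**

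In a simulation of 1,000,000 patients allocated 60:40, with a true co-treatment effect of 0.50 and an uptake difference of 17.6 points, the unadjusted estimate was 0.498 and the adjusted estimate 0.473. The true direct effect was 0.50 − 0.176 × 0.50 = 0.412, so the adjusted figure matches neither quantity. The co-treatment coefficient came out at 0.144 instead of 0.50. With no arm effect on uptake, the adjusted estimate stayed at 0.498 even with severity present.

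The sums are for HbA1c. The same algebra applies to PHQ-9 but was not run.

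**The case against.** A reader might infer that the primary models do adjust for on-treatment values, so that part of the HOPE effect is certain to be lost. The protocol does not support that.

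- No sentence says that the 6- or 12-month values enter the models, and baseline versions of the same variables are built too.
- Two of the three model terms are not the constructed variables. Being on insulin and taking psychotropics are statuses, whereas the constructed versions record insulin added and psychotropics started or changed. Only the psychotherapy term matches. In the a priori list insulin sits between the baseline outcome values and site, so baseline status is a natural reading.
- The Exclusion Criteria sentence follows one about patients in mental health care at recruitment, and may mean treatment at entry.
- The route through coaching is possible but not shown. Referral requests and medication changes stay with the PCP, the referral examples given are a diabetes educator and a nutritionist, and both arms receive the mental health prompt.
- Covariate timing is often left to a statistical analysis plan, which is not available here.

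The first four points stand, and they make the bias conditional. The power losses above may also be too large, because they use the unadjusted SD. If baseline and outcome correlated at 0.6 (an assumption), the residual SD would be 1.1 × 0.8 = 0.88 and power at any given effect would be higher.

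The last point does not dispose of the matter. The protocol does not leave the covariates open: it names them and does so inconsistently, next to visit-specific variables that an analyst could reasonably take to be the model terms.

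**Conclusion.** The concern holds in conditional form. The Aim 1 covariate set is stated inconsistently, and three of its terms are not tied to baseline although post-randomisation versions are expressly built. If those versions are used and coaching changes co-treatment, the treatment coefficient is no longer the total effect of HOPE versus EUC.

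The documents determine neither the size nor the direction. Against a true 0.50, the assumed scenarios give 0.26 to 0.54. Confounding by severity brought the simulated estimate closer to the total effect (0.473 at a 17.6-point shift). If uptake does not differ between arms and is not confounded, there is no bias. These figures rest on assumed uptake differences and co-treatment effects, a linear model without interaction, and the SD of 1.1 in G1. They show why the wording matters and do not predict the trial's result. The point is a free improvement.

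**What to change.** 1. In G2, state one covariate set for the 6-month, 12-month and longitudinal Aim 1 models, measured before randomisation: baseline HbA1c or PHQ-9, insulin use at baseline, psychotherapy at baseline, psychotropic use at baseline, and site. In the longitudinal model the baseline outcome is already the first response and need not be entered again as a covariate.
2. Say which baseline psychotropic variable is meant, since taking a drug and having one started or changed in the previous 6 months differ.
3. Bring the a priori list in G2 into line with this set, so that psychotherapy and medication are not compared in one place and adjusted for in another.
4. Use the 6- and 12-month co-treatment variables only in descriptive tables by arm or in the exploratory mediator analyses.
5. Limit the covariate sentence under Exclusion Criteria to treatments and service use at baseline.

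The cost is wording only. Baseline versions of the co-treatment variables are already planned, and medication use is among the baseline characteristics. The sample size and the assessment schedule do not change.
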